#### Secondary endpoints

Cervical infection with HPV-16 and/or HPV-18 over 12 months (measured by two tests with an interval of 12 months), *defined as at least one positive HPV-16 or HPV-18 DNA PCR assay at the additional visit in 12 months after getting the positive HPV-16 or HPV-18 test result at enrollment (Month 0) or follow-up (Month 36) or any additional screenings during the study period.*

Cervical infection with 12 other high-risk HPV besides of type 16/18 (by PCR), *defined as at least one positive for HPV 31/33/35/39/45/51/52/56/58/59/66/68 or multiple types DNA PCR assay at enrollment (Month 0) or follow-up (Month 36) or any additional screenings during the study period.*

Any cervical lesions or diseases in birth cohorts, *defined as atypical squamous cells of undefined significance (ASC-US), atypical glandular cells (AGC), atypical squamous cells, cannot exclude for highly squamous intraepithelial lesions (ASC-H), low-grade squamous intraepithelial lesion (LSIL), high-grade squamous intraepithelial lesion (HSIL), Cervical Intraepithelial Neoplasia (CIN) 1, CIN2, CIN3, squamous cell carcinoma (SCC), adenocarcinoma *in situ* (AIS) and adenocarcinoma (ADC). Any hr-HPV type infection is defined as at least one positive for HPV 16/18/31/33/35/39/45/51/52/56/58/59/66/68 or multiple types DNA PCR assay in the aforesaid cervical sample.*

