### Exclusion criteria

The following criteria should be checked at the time of study entry. If any apply, the subjects must not be included in the study:Pregnancy at the enrollment.Females with historical cervical diseases (i.e., cervical intraepithelial neoplasia (CIN)1, CIN2, CIN3, and cervical cancer) before the recruitment.After hysterectomy.Females with malignant tumor history or other severe diseases (e.g., liver failure, heart failure, etc.), whose life expectancy is less than 12 months.Females who (1) have historical HPV vaccination, or (2) are in non-exposed groups but have clear intention for HPV vaccination in next 3 years (confirmed by field investigators before enrollment).Any high-risk HPV (hr-HPV) DNA (i.e., HPV 16/18/*31/33/35/39/45/51/52/56/58/59/66/68*) positive result at baseline.Having abnormal colposcope diagnosis or cervical diseases at the baseline screening (women tested HPV positive or having abnormal colposcope diagnosis or cervical disease will be followed up and managed through the local referral system).

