**Fig. 2 Fig2:**
[figure not shown]
Study procedure

Subjects will be stratified into three age groups (9–20 y/o, 21–30 y/o and 31–45 y/o) and divided into exposed and non-exposed groups by vaccination status. The exposed group will include subjects who received 1 or 2 doses of *Cervarix* and the non-exposed group will include subjects who did not receive any doses of HPV vaccine.

During the study period, two visits will be scheduled for all subjects at Month 0 and Month 36, which means the follow-up period will be 3 years. In the first visit, the questionnaire survey will be administrated for all the subjects to obtain the demographic information, sexual history, menstrual and obstetrical histories, etc. For the ones who are eligible for the cervical cancer screening (i, Have sexual debut at the enrollment; ii, no contradiction of screening and iii, are willing to undergo the screening), the type-specific HPV DNA PCR testing will be given within 2 weeks after the enrollment. After 3-years follow-up, the subjects will be called back for the second visit. A questionnaire which measures any changes of behavior during the follow-up period will be performed. Then the second screening with type-specific HPV DNA PCR testing will be given within 2 weeks after the call-back.

At each visit, type-specific HPV DNA PCR testing will be the primary screening approach, and for the ones with unsatisfactory findings (i.e., hr-HPV infection) will be referred to the local abnormal cervical cancer screening results management system for further medical activities (Fig. 1)

By the end of the follow-up period, the prevalence of the HPV infection, cervical disease (e.g., CIN1, CIN2, CIN3, SCC, AIS, etc.) will be described in each birth cohort by their exposure status. If the sample size is sufficient, the effectiveness of *Cervarix* will be assessed as the exploratory objective.

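### The 12-month HPV 16/18 infection endpoint does not require the same type at both tests, and its Month 0 and Month 36 entry points do not fit the baseline exclusion and the 3-year follow-up

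*Protocol article*

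**What the plan says.** The protocol article, under Secondary endpoints, describes this endpoint as "measured by two tests with an interval of 12 months". An event is a positive PCR for either type "at the additional visit in 12 months after getting the positive HPV-16 or HPV-18 test result at enrollment (Month 0) or follow-up (Month 36"), with extra screenings as a third place where the first positive may arise. So the second test need only show "at least one positive HPV-16 or HPV-18 DNA PCR assay at the additional visit in 12 months", and the first is any positive for either type. Nothing links the type found at the second test to the type found at the first.

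Three other parts of the article bear on it:

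- **Exclusion criteria.** "Any high-risk HPV (hr-HPV) DNA", with types 16 and 18 in the list, excludes a woman if there is a "positive result at baseline". The same section adds that "women tested HPV positive or having abnormal colposcope diagnosis or cervical disease will be followed up and managed through the local referral system".
- **Study procedure.** It states that "two visits will be scheduled for all subjects at Month 0 and Month 36, which means the follow-up period will be 3 years". Study design and setting likewise gives two visits per participant. The assay at both is type-specific.
- **Background.** In the local screening programme, women who test HPV-negative are invited again only after 3 years.

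**The concern.** An endpoint that needs two positive tests a year apart is meant to capture infection that lasts. The Abstract supports this, since it names the continuous status of infection as something to be studied. Without a same-type condition, the definition also counts a woman who cleared one type and acquired the other. A vaccine could affect those two processes differently, so mixing them blurs what the result means.

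The timing raises a separate problem. If the two visits that every woman attends cannot start a 12-month pair inside the stated follow-up, the endpoint is observed only in women who happened to be screened between visits and were then tested again. A by-group description would then depend partly on who sought screening and who returned, as well as on infection.

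**Working it through.** The protocol gives no sample size or event count for this endpoint. The only computed figures are those of Table 1, for the primary HPV 16/18 infection endpoint. They are checked first because the expected number of infections comes from them.

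**1. Table 1.** Inputs from Sample size: incidence p1 = 0.02 in the non-exposed; effectiveness 83%, 66% and 50%; 1:1 groups; α = 0.05 (two-sided assumed); power 0.80; 30% loss. With p2 = p1 × (1 − VE) and p̄ = (p1 + p2)/2, the pooled two-proportion formula without continuity correction is

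n = [1.96·√(2p̄(1 − p̄)) + 0.842·√(p1(1 − p1) + p2(1 − p2))]² / (p1 − p2)²

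| Age group | p2 | n recomputed | n in Table 1 | Recruitment, 2 × ⌈n in Table 1 / 0.7⌉ |
|---|---|---|---|---|
| 9–20 | 0.0034 | 658 | 661 | 1890 |
| 21–30 | 0.0068 | 1190 | 1208 | 3452 |
| 31–45 | 0.0100 | 2319 | 2371 | 6776 |

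The group sizes agree within 3%, and the recruitment total of 12,118 is exact.

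**2. Expected infections, both groups together.** Per age group this is n × 0.02 × (1 + (1 − VE)):

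- 9–20: 661 × 0.02 × 1.17 = 15.5
- 21–30: 1208 × 0.02 × 1.34 = 32.4
- 31–45: 2371 × 0.02 × 1.50 = 71.1
- Total: 119.0 among 8,480 women

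This assumes that every evaluable woman is tested and that the 2% applies over the follow-up, a period that Table 1 does not state.

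**3. Type rule.** Take a woman positive for 16 only at the first test and for 18 only twelve months later. Both tests are positive for 16 or 18, so the definition is met, yet neither type was detected twice.

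**4. Timing.** If the first positive is at month t, the second test falls at t + 12. It lies inside the 36-month follow-up only if t ≤ 24.

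| First positive | Second test | Position |
|---|---|---|
| Month 0 | Month 12 | Excluded at baseline, so no index case |
| Month 36 | 36 + 12 = Month 48 | 12 months after follow-up ends |
| Unscheduled, t ≤ 24 | Month 36 or earlier | Inside follow-up, if retested |
| Unscheduled, 24 < t < 36 | After Month 36 | Outside follow-up |

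The two scheduled tests are 36 months apart, so they cannot form the pair themselves. Women not screened at Month 0 have no Month 0 result and do not reopen that route.

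**5. How many women the Month 36 row concerns.** The documents do not give the share of infections first found at Month 36. As an assumption only, shares of 50% and 90% would mean 119 × 0.5 ≈ 60 and 119 × 0.9 ≈ 107 women whose retest falls at Month 48.

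**The case against.** **Month 36.** A reader might infer that a Month 36 positive can never become an event, or that the endpoint is empty. The documents do not support that. The definition itself names an additional visit. The two visits are those scheduled for all women, which leaves room for a conditional one. The Abstract and Strengths of the study say that the regional health platform (YRHIP) goes on monitoring outcomes afterwards. Unscheduled screenings also remain as a third route. The two figures are not visible, so a later test drawn there cannot be ruled out. What stands is narrower: no text extends data capture for this endpoint past 3 years. Reading the study period as calendar time does not settle it. With 24 months of recruitment, it would span 24 + 36 = 60 months, and only women enrolled in about the first 12 months could reach Month 48.

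**Detail left to other documents.** Windows and cut-offs are commonly left to a full protocol or SAP, so their absence alone would be no finding. Here, however, the article fixes a type rule and entry points that conflict with its own design.

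**Month 0.** The same wording appears in the primary endpoint and in the endpoint for the 12 other high-risk types. This is correct, and the repair must cover all three.

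**Size of the type problem.** Type replacement may be rare. Assume that the 2% is either a 3-year or an annual risk and that new infections are independent. New HPV 16/18 infections in 12 months among 119 positives would then be about 119 × 0.02/3 = 0.8 to 119 × 0.02 = 2.4, and fewer for the other type alone. Women already infected may be at higher risk, so this is not an upper limit. The number is unknown, but the definition is still wrong.

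**Consequence.** A reader might also infer that an effectiveness estimate is biased. The regression models in Statistical analysis name HPV 16/18 and HPV 31/33/45 infection, not this endpoint, so on the text the by-group description is what is affected.

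**Conclusion.** The point holds in this form. The definition lacks a same-type condition. Its Month 0 entry contradicts the baseline exclusion. Its Month 36 entry needs a Month 48 result that the stated follow-up does not cover. Within 36 months only an unscheduled positive by about Month 24, with a later retest, can count. This rests on reading the interval as about 12 months, as the endpoint's own description says. Reading it as within 12 months does not help, because any retest after Month 36 is still outside follow-up.

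About 119 infections in total is the scale implied by Table 1. It is tempting to say that most of these would go unclassified. That is an inference from the two-visit schedule and the 3-year recall, because the documents give no frequency of interim screening. The sample size and the regression analyses named in the article are not affected. For a secondary endpoint, this should be corrected before the data are extracted.

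**What to change.** - **Type.** Define an event as type 16 at both tests or type 18 at both, about 12 months apart, with a stated window. The assay is already type-specific, so no new test is needed.
- **Month 0.** Remove it as an entry point, and reconcile the Exclusion criteria with the primary endpoint, this endpoint and the other high-risk HPV endpoint in one change.
- **Cut-off.** Set the YRHIP data cut-off for this endpoint at Month 48 plus the window, and say so in Study procedure.
- **Missing retests.** Report by group how many women were positive and how many were retested. Treat positives without a retest as missing, not as non-persistent. For example, with P confirmed, U not retested and N women at risk, give the bounds P/N and (P + U)/N. Scoring the U women as non-persistent would report only the lower bound, and unequal retesting would then distort the comparison.

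The cost is endpoint wording and a later platform extract for up to about 120 women. The downside is that this one secondary endpoint is reported about a year later. It also remains dependent on retest completeness, because results captured from routine care do not remove selection by who returns; the bounds only show how much that could matter. Table 1 does not change, and nothing here asks for a change in how positive women are managed.

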**Methods:**

This is a prospective, multi-age birth cohort study to investigate the incidence and continuous status of HPV infection, and relevant cervical diseases by exposure status (with *Cervarix* vaccination history or without any HPV vaccination history). It is planned to recruit 12,118 eligible women at age of 9 to 45 years from vaccination clinics or hospital outpatient clinics, and then follow up them for three years. The standard questionnaire will be used to collect information such as demographic characteristics, menstruation and obstetrical histories, history of sexual behavior, personal behavior history, history of disease and pathogen infection, medication history, and family history at baseline. After three years, the changes of these behaviors will be investigated again, and other related health status information will be retrieved from the electronic health records during the follow-up period. If available physically and legally, the cervical cancer screening will be performed, including type-specific HPV deoxyribonucleic acid (DNA) polymerase chain reaction (PCR) testing and contingent thinprep cytologic test (TCT) and colposcopy. The free cervical cancer screening will be captured and uploaded timely to the Yinzhou Regional Health Information Platform (YRHIP); therefore, the long-term outcomes of participants will be monitored.

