## Background

Cervical cancer was the fourth most common cancer in women, with approximately 0.60 million cases and over 0.34 million deaths from cervical cancer worldwide in 2020 [1]. China is one of the countries with the most cases contributed with approximately 0.11 million cases and 0.05 million deaths [2]. Further, both the incidence of cervical cancer and disease burden still increased in the last decades, and its onset age becomes much younger in Chinese women [3, 4]. Human Papillomavirus (HPV) infection is the primary cause of cervical cancer [5], specifically, HPV16 and 18 infections accounted for 84.5% of invasive cervical cancer in China [6].

Expanding the coverage of HPV vaccines is an essential part of the 90–70-90 target proposed by the World Health Organization (WHO) for eliminating cervical cancer [7]. In a modeling study, with 70% coverage of bivalent vaccine, cancer cases can decrease by 58% to 33% in rural areas and 69% to 32% in urban areas at ages of 12 to 55, respectively [8]. China has also been making effort to increase vaccination coverage. Since 2016, HPV vaccines have been introduced for females aged 9–45 in mainland China, such as *Cervarix* (9–45 years old) in 2016, *Gardasil 4* (20–45 years old) in 2017, *Gardasil 9* (16–26 years old) in 2018 and the domestic bivalent HPV vaccine *Cecolin* (9–45 years old) in 2019 [9–12]. These vaccines were not included in the programmed immunization and were paid for by the receivers. Since 2020, some of cities in China have launched free HPV vaccination programs for girls under 14 years, which only included the domestic bivalent HPV vaccine *Cecolin* for now [13, 14]. In addition, China is also popularizing cervical cancer screening to accelerate the elimination of cervical cancer. China has initiated *the Two Cancers (the cervical cancer and breast cancer)* Screening Program in 2009, which provided females aged 35 years and over with cervical cancer and breast cancer screening for free [15]. Screening strategies varied across regions, including HPV-initiated and TCT-initiated tests. As for Yinzhou, Ningbo, where our study will be conducted, the standard cervical cancer screening process initiate with a type-specific HPV DNA PCR testing, and for the ones with HPV infection will be referred to colposcopy or cytology test, while those who are tested negative will be invited for another screening after 3 years (Fig. 1).

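### The lesion endpoint is worded as the incidence of any cervical lesion in the birth cohorts, but cytology and colposcopy at study visits follow only a positive hr-HPV PCR

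*Protocol article*

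**What the plan says.** The third secondary endpoint opens "Any cervical lesions or diseases in birth cohorts, *defined as atypical squamous cells of undefined significance (ASC-US), atypical glandular cells (AGC" and continues through the remaining cytology grades and CIN1 to CIN3 to invasive cancer. Its list of qualifying abnormalities sets no condition on HPV status. The second objective under Aims is to describe the incidence of such lesions by exposure status.

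Three places describe how lesions come to be found:

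- Abstract, Methods: screening is type-specific HPV PCR with "contingent thinprep cytologic test (TCT) and colposcopy".
- Background, on the local pathway: "for the ones with HPV infection will be referred to colposcopy or cytology test, while those who are tested negative will be invited" to another screening after 3 years.
- Study procedure: at each visit PCR is the primary approach, and "for the ones with unsatisfactory findings (i.e., hr-HPV infection) will be referred to the local abnormal cervical cancer screening results management system".

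The Exclusion criteria remove women with an hr-HPV "positive result at baseline.Having abnormal colposcope diagnosis or cervical diseases at the baseline screening". Baseline screening is offered only to women who have had sexual debut, have no contraindication and are willing.

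The measure is also named in two ways. Aims and Statistical analysis speak of incidence, whereas Study procedure says that "the prevalence of the HPV infection, cervical disease (e.g., CIN1, CIN2, CIN3, SCC, AIS, etc.) will be described in each birth cohort".

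**The concern.** The endpoint covers the whole cohort, but the examination that reveals it is given to a subset chosen by PCR result. A PCR-negative woman has no scheduled cytology at either visit, and an unscreened woman has no test at all. If both stay in the denominator, they count as free of lesions unless an unscheduled record says otherwise. Nor do women retained after baseline have protocol cytology at Month 0, so a lesion found later cannot be shown to be new.

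The chance of being examined also depends on an outcome that the vaccine is expected to change. Fewer vaccinated women become HPV 16/18 positive, so fewer are sent for cytology. A chance cytological finding that the vaccine does not affect would then be recorded less often in the exposed group. The Statistical analysis section describes group differences in relevant disease by exposure status, names Chi-squared tests for categorical data, and plans Kaplan–Meier curves for each endpoint. The lesion comparison will therefore be visible, and the limitations section does not warn about this.

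**Working it through.** **Inputs.** From Table 1: HPV 16/18 proportion 0.02 in the non-exposed; effectiveness (VE) 0.83, 0.66 and 0.50; and 661, 1208 and 2371 women per arm. The proportion with other hr-HPV types, p, is not given. I assume 5%, 10% and 15%, equal in both groups. I also assume that every woman counted is PCR-tested and every positive woman is examined.

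**Table 1 first.** A two-sided two-proportion calculation (α 0.05, power 0.80, pooled variance, no continuity correction) with p1 = 0.02 and p2 = 0.02 × (1 − VE) gives 658, 1190 and 2319 per arm. The stated figures are 0.5%, 1.5% and 2.2% higher. They are not in dispute. No sample size is stated for the lesion endpoint.

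**Fewer work-ups per exposed arm** = n × 0.02 × VE:

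- 9–20 years: 661 × 0.02 × 0.83 = 11.0
- 21–30 years: 1208 × 0.02 × 0.66 = 15.9
- 31–45 years: 2371 × 0.02 × 0.50 = 23.7

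The total is about 51.

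**Relative shortfall**, with no overlap between types. Non-exposed referred = n × (0.02 + p). Exposed referred = n × (0.02 × (1 − VE) + p). Shortfall = 0.02 × VE / (0.02 + p).

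| Age group | p | Non-exposed referred | Exposed referred | Shortfall |
|---|---|---|---|---|
| 9–20 | 5% | 46 | 35 | 24% |
| 9–20 | 10% | 79 | 68 | 14% |
| 9–20 | 15% | 112 | 101 | 10% |
| 21–30 | 5% | 85 | 69 | 19% |
| 21–30 | 10% | 145 | 129 | 11% |
| 21–30 | 15% | 205 | 189 | 8% |
| 31–45 | 5% | 166 | 142 | 14% |
| 31–45 | 10% | 285 | 261 | 8% |
| 31–45 | 15% | 403 | 379 | 6% |

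If infections with different types are instead independent, referred = 1 − (1 − HPV 16/18 proportion)(1 − p). The shortfalls in age order are then 23%, 18% and 14% at p = 5%; 13%, 10% and 8% at p = 10%; and 8%, 7% and 5% at p = 15%. The direction does not change.

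**Share without protocol cytology or colposcopy** (no-overlap model). Non-exposed: 1 − 0.17 = 83% to 1 − 0.07 = 93%. Exposed: 84% (31–45 years, p = 15%: 1 − 0.16) to 95% (9–20 years, p = 5%: 1 − 0.0534).

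**Which lesions the shortfall distorts.**

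- Caused by HPV 16/18: they fall because infection falls. That is a real effect.
- Caused by the other 12 types: those women are PCR-positive and referred at the same rate in both groups under this model, so the spurious reduction is zero.
- Independent of all hr-HPV types: found only when the woman happens to be PCR-positive, so detection falls by the percentage in the last column.

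**Scale within the pooled endpoint.** If 2% to 10% of the 51 missing work-ups would have shown an HPV-independent abnormality (an assumption), 51 × 0.02 to 51 × 0.10 is about 1 to 5 women over all cohorts. Non-exposed women worked up number 4240 × 0.07 = 297 to 4240 × 0.17 = 721.

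**The case against.** The strongest defence has five parts.

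- **Size.** A reader might infer that every lesion not caused by HPV 16/18 is understated by 6% to 24% in the vaccinated group. The model does not support that: lesions due to other hr-HPV types are found equally in both groups. This part stands, and it confines the bias to HPV-independent abnormalities.
- **Other sources of data.** YRHIP supplies self-initiated screening and cervical treatment whatever the study PCR shows, so PCR-negative women are not lesion-free by construction. This stands as a limit on the wording. Such records are unscheduled, and their frequency may differ by vaccination status, so they do not close the gap.
- **Timing.** Follow-up is fixed by two visits, "which means the follow-up period will be 3 years", and the second PCR comes after call-back. A reader might infer that work-ups triggered at Month 36 are lost. The document sets no such data cut, and its 12-month persistence endpoint already uses tests made after a Month 36 positive. No error is shown here.
- **Descriptive aim.** Effectiveness is an objective only for HPV 16/18, and the regression does not cover lesions. This is correct and lowers the stakes, but the comparison by exposure is still planned.
- **Endpoint text.** The endpoint paragraph ends by defining any hr-HPV infection in the same cervical sample, which might hint at a restriction to positive women. It defines infection, however, and does not limit which lesions count.

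HPV-primary screening is the local pathway and is not criticised. The screening figures are not shown, but the text in three places agrees.

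**Conclusion.** The concern holds as a fault of wording and ascertainment in a secondary endpoint, and it should be corrected before analysis. As defined, the endpoint will not yield an incidence of any lesion in the birth cohorts. It would go too far to say that no incidence can be had: a rate of screen-detected lesions in hr-HPV-positive women, over all PCR-tested women, remains estimable.

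The difference in examination is about 11, 16 and 24 women per arm, on Table 1's 2% and its assumed effectiveness, with infections of different types not overlapping. The spurious reduction of roughly 6% to 24% applies only to abnormalities independent of all hr-HPV types, mainly incidental cytology such as ASC-US or AGC. It rests on the assumed 5% to 15% for other types. The bias in the pooled endpoint is smaller than this, and its size cannot be derived from the document.

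**What to change.** 1. Redefine the endpoint as screen-detected cervical lesions in hr-HPV-positive women, with all PCR-tested women as the denominator, and stop describing it as any lesion in the cohort.
2. Report histological disease (CIN1, CIN2, CIN3, AIS, cancer) separately from cytology-only findings, and draw no vaccine conclusion from the cytology-only part. Redefinition alone does not remove the unequal examination for incidental cytology.
3. Show by exposure and age group the numbers PCR-tested, hr-HPV positive, referred and examined.
4. Reconcile incidence (Aims, Statistical analysis) with prevalence (Study procedure).
5. State, as a clarification, that results of work-ups triggered by the Month 36 PCR are counted.
6. Add the contingent examination to the limitations.

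The cost is a change of wording and some extra tabulation. No additional procedures are needed and the sample size is unchanged. The downside is a narrower endpoint with fewer events.
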